#### Reproducibility

We will deposit the final protocol in a preprint repository (medRxiv.org) and submit it to a peer-reviewed journal. At publication of the primary results, the full protocol, the data management plan including the codebook of the trial database, and information on how to get access to the primary trial data will be published in the repository of the University of Bern which fulfills the FAIR criteria (Bern Open Repository and Information System (boris.unibe.ch)). A 12-month grace period after publication of the primary results is currently foreseen to allow all collaborators to complete additional, pre-planned analyses and projects.

#### Interim analyses

We will conduct one interim analysis after endpoint data were completely collected for 200 clusters. We will reassess the ICC based on the data collected to adjust the sample size if needed. To calculate the ICC, we will use multilevel mixed-effects logistic regression. If the ICC is > 0.024, we will perform new power calculations using the same assumptions as in the original sample size calculation. Based on these calculations, we will increase the number of clusters and/or the number of patients per cluster except if the required increase would be too large to be feasible. Because the type I error is not affected by the recalculation of the ICC, we will not adjust the significance level.

Moreover, an interim analysis of the primary outcome will be performed to examine the trial for potential futility: The conditional power for a statistically significant difference between the intervention and control groups at the end of the study will be estimated based on data collected at the time of the interim analysis. If the conditional power is < 20%, it is recommended to terminate the trial for futility. Implications for type I and II errors are minimal, so no adjustment is needed for this type of interim analysis [45].

Given that no interim analysis for safety or efficacy will be done, no independent Data Monitoring Board (iDMC) is established, and possible sample size adaptations or trial termination for futility will be decided by the Steering Committee.

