### Statistical analysis plan and sample size calculation

#### Sample size calculation

Sample size calculations were based on the primary objective, i.e., whether patients in the StOP? intervention group have a lower risk of mortality compared to patients in the standard of care group. The primary effect measure will be odds ratio as the primary analysis will be based on a logistic regression (see below). Based on the data from the first StOP? study, we calculated an intracluster correlation coefficient (ICC) of 0.024 from a mixed-effects logistic model. Also, we estimated 30-day mortality from the before phase of the StOP? study and use this number (1.8%) for the event rate in the control group. The target treatment effect that we do not want to miss is an odds ratio of 0.5, i.e., we aim to reduce mortality in the StOP? intervention group to 0.9%. Sample size calculations were done in Stata (release 16.1) using the power twoproportions command with the cluster option. The command calculates power based on a *z*-test with standard error adjusted by the intracluster correlation and varying cluster size. With 400 clusters overall (with 1:1 allocation, i.e., 2 × 200), an average size of 24 patients per cluster, and a coefficient of variation of 0.5, we will achieve 84% power at a significance level of 0.05 (two-sided).

We assume that some patients will be operated by two disparate surgeons (i.e., two surgeons randomized to different trial arms are performing one operation jointly). To accommodate this, we fixed the target average cluster size at 30 patients. This sample size allows for varying cluster sizes to accommodate differences in operation volume across clusters (coefficient of variation of 0.5, i.e., cluster size is allowed to range between 10 and 50 patients). A minimum of 12,000 patients will be required. Based on the experience of the StOP? I study, we expect that some surgeons perform many more operations than the assumed upper cluster size. Therefore, we expect that 14,000 patients will be enrolled overall. Given the relatively low number of events, we performed simulation studies to check the robustness of the assumption of an asymptotically normally distributed test statistic. Using a random-effects logistic regression in 1000 simulated trials with the same assumptions as described above, we calculated a power of more than 90%.

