We also performed several sensitivity analyses to account for the uncertainty of our assumptions, e.g., (1) allowing for a larger variation in cluster size (coefficient of variation of 0.7) results in 82% power; (2) allowing for the unlikely case of higher intracluster correlation (ICC of 0.03) results in 80% power; and (3) allowing for enrolment problems i.e., 370 clusters but similar cluster size results in 80.9% power or a similar number of clusters but smaller average cluster size (21 patients) results in 80.6% power.

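### The interim sample-size check reacts to the ICC alone and keeps the planned cluster-size inputs, so the recalculated number of clusters can be off in either direction

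*Protocol article*

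**What the plan says.** The section on interim analyses sets the timing: "We will conduct one interim analysis after endpoint data were completely collected for 200 clusters". It names one quantity to update: "We will reassess the ICC based on the data collected to adjust the sample size if needed". The trigger and the inputs follow: "If the ICC is > 0.024, we will perform new power calculations using the same assumptions as in the original sample size calculation". The permitted response is to add clusters, operations per surgeon, or both, unless the increase needed is not feasible. No target power is given for the recalculation.

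The original assumptions are in the section on sample size calculation: "With 400 clusters overall (with 1:1 allocation, i.e., 2 × 200), an average size of 24 patients per cluster". The CV is set at 0.5, and the stated power is 84% at a two-sided 5% level. The ICC is 0.024, control mortality 1.8% and the target odds ratio 0.5.

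The same section treats cluster size as uncertain. Its sensitivity analyses vary the CV (0.7, 82% power), the ICC (0.03, 80%), the number of clusters (370, 80.9%) and the mean size: "a similar number of clusters but smaller average cluster size (21 patients) results in 80.6% power". It also says that "we expect that some surgeons perform many more operations than the assumed upper cluster size", and on that basis expects 14,000 patients rather than the required minimum of 12,000.

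**The concern.** The recalculation is the only planned adjustment of sample size, and its purpose is to protect power. Power here depends on the ICC, the mean number of analysable operations per surgeon, the CV of that number and the number of surgeons. The interim rule updates the first and freezes the mean and CV. Yet these two are the easiest to know at that point: they are counts in 200 completed clusters, need no outcome model and reveal nothing about the treatment effect.

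The trigger also fits poorly with the plan's own figures. A mean of 21 and an ICC of 0.03 cost about the same power (80.6% and 80%), but only the second leads to any action.

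Two things are at stake. If clusters are smaller or more uneven than planned while the ICC stays at or below 0.024, the rule does nothing. If the ICC is higher, the new number of clusters is worked out for a cluster-size distribution that may differ from the one already observed. The point concerns cluster size only, not the assumed mortality rate.

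**Working it through.** **Inputs from the sample size section.** Control risk p1 = 0.018. Odds ratio 0.5 gives odds of 0.5 × 0.018/0.982 = 0.009165, so p2 = 0.00908. K = 400 clusters in total, mean size m = 24, CV = 0.5, ICC = 0.024, two-sided α = 0.05.

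**Formula.** The article names the software command (a z-test for two proportions, adjusted for ICC and varying cluster size) but prints no formula. I used the relative-efficiency form for unequal clusters:

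- L = m·ICC / (m·ICC + 1 − ICC)
- design effect DE = [1 + (m − 1)·ICC] / [1 − CV²·L·(1 − L)]
- effective n per arm = (K/2)·m / DE
- power = Φ[(p1 − p2 − 1.96·se0)/se1], with se0 the pooled and se1 the unpooled standard error.

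**Base case.** L = 0.576/(0.576 + 0.976) = 0.371. DE = 1.552/(1 − 0.25 × 0.371 × 0.629) = 1.552/0.942 = 1.648. Effective n = 200 × 24/1.648 ≈ 2,912 per arm. Then p1 − p2 = 0.00892, se0 = 0.00303 and se1 = 0.00303, so z = (0.00892 − 0.00594)/0.00303 ≈ 0.985 and power is 83.8%.

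**The plan's figures reproduce.**

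| Case | Stated | Recomputed |
|---|---|---|
| Base | 84% | 83.8% |
| CV 0.7 | 82% | 81.5% |
| ICC 0.03 | 80% | 80.5% |
| 370 clusters | 80.9% | 80.9% |
| Mean 21 | 80.6% | 80.6% |

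**ICC at 0.024, so no recalculation (400 clusters).** With mean 21 and CV 0.7 together, L = 0.341, DE = 1.480/0.890 = 1.663 and effective n ≈ 2,526 per arm. Power is 78.3%, and 462 clusters would be needed to return to 83.8%. For contrast, an ICC of 0.0241 with the planned cluster sizes lowers power by less than 0.1 point and does trigger the rule.

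**ICC at 0.03, so the rule acts.** The planned inputs (24, CV 0.5) give DE = 1.690/0.939 = 1.800, and 438 clusters restore 83.8%. Against other observed cluster sizes:

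| Observed mean, CV | Clusters needed for 83.8% | Power with 438 |
|---|---|---|
| 24, 0.7 | 466 | 81.5% |
| 21, 0.5 | 472 | 81.0% |
| 21, 0.7 | 504 | 78.5% |
| 28, 0.5 | 402 | 86.8% |
| 28, 0.7 | 430 | 84.5% |

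The mean of 28 is an illustration built from the plan: 14,000/400 = 35 per surgeon, less the 20% implied by going from 30 to 24 for mixed-arm operations, is 35 × 0.8 = 28. The shortfall at (21, 0.7) is 504 − 438 = 66 clusters. The excess at (28, 0.5) is 438 − 402 = 36.

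**Dependence on the target.** The 83.8% target is my assumption, because the plan names none. With an 80% target at ICC 0.03, the planned inputs need 396 clusters, so the rule would add none, while (21, 0.7) would need 456.

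**The case against.** A reader might infer that the recalculated number of clusters is simply wrong, or that the trial will drop below 80% power without anyone noticing. The documents do not support either reading, for these reasons.

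- **The expected departure is upward.** The plan foresees more operations, concentrated in busy surgeons. That raises mean and CV together, and the effects largely cancel: 28 with CV 0.7 needs 430 clusters against the rule's 438, and 400 clusters give 84.8% at ICC 0.024. The excess of 36 appears only if the CV stays at 0.5.
- **The harmful case stacks two departures.** Each one in the plan's sensitivity analyses keeps about 80% power on its own. The 78.3% combines two of them.
- **The z-test may be conservative.** The plan reports more than 90% power from simulation with a random-effects logistic model under the base assumptions. A z-test value of 78% therefore does not prove that the planned analysis falls below 80%.
- **Cluster size is visible during the trial.** Basic operation data are collected weekly and the steering committee meets at least biweekly.
- **The first 200 clusters may not represent the rest.** Units are grouped by geography, and joint operating ranges from 5% to 90% of procedures by hospital type.
- **An ICC-only rule is at least clear and prespecified.**

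The first five points stand as limits on the size and certainty of the error. They do not remove the point. None of the monitoring described feeds cluster size into the recalculation, and the article positively fixes both trigger and inputs rather than leaving them to an analysis plan. Imperfect representativeness calls for caution in projecting the observed counts; it does not make the original guesses a better input.

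**Conclusion.** The point holds as a conditional weakness. The interim rule responds to one of the uncertain inputs and keeps planning values for two others that can be counted by then. Its answer can miss in either direction: at ICC 0.03, from 66 clusters too few (mean 21, CV 0.7) to 36 too many (mean 28, CV 0.5), with almost no error at 28 and CV 0.7. With no trigger, the adverse combination costs about 5.5 points (83.8% to 78.3%).

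These sizes rest on the z-test formula, an assumed target of 83.8% and assumed observed cluster sizes, since the article gives no observed ones. They show that the rule can lead to a poorer decision, not that it will. Changing it is a cheap improvement rather than the repair of a fault that threatens the trial.

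**What to change.** Replace the ICC trigger in the interim analyses section with wording such as: *At the interim, power is recalculated whatever the ICC, using the re-estimated ICC, the observed mean number of analysable operations per surgeon, the observed CV and the expected final number of clusters, all pooled over arms. The result is compared with a target power of [value to be stated]. If the required increase is not feasible, the expected power is restated.* Where the remaining sites differ in hospital type from the first 200 clusters, say how the observed mean and CV are projected to them.

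The cost is a few lines of text. The added inputs are counts pooled over arms and say nothing about the treatment effect, so the plan's reasoning for leaving the significance level unadjusted is unaffected. The downsides are that the restated power may be below 84%, and that the first 200 clusters may not fully represent later ones.

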## Methods/design

### Objectives

The main objective of the trial is to test if performing the StOP?-protocol improves patient outcomes after operations. The underlying rationale is that by influencing clinical communication within the surgical team during the operation, the StOP?-protocol may improve the quality and safety of surgical care and thereby reduce post-operative mortality and morbidity.

The primary hypothesis is that the consistent use of the StOP?-protocol by the main surgeon reduces patient mortality within 30 days after an operation.

The secondary hypothesis is that the consistent use of the StOP?-protocol by the main surgeon reduces unplanned reoperations and unplanned readmissions up to 30 days after the index operation, and reduces the length of hospital stay.

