#### Statistical method for primary and secondary outcomes

The primary analysis will follow the intention-to-treat (ITT) principle. We will assess outcomes at the patient level, accounting for the correlated nature of data within surgeon and hospital by using multilevel mixed-effects models. The primary outcome (30-day mortality) will be presented as a number and proportion for each group. We will incorporate random intercepts for surgeons and units in the multilevel models and adjust for variables related to the site, surgeon characteristics, and type of operation. The odds ratio of death for the intervention vs. the control group will be presented with a two-tailed 95% confidence interval (CI) and accompanying *p*-value. The primary null hypothesis of no difference in mortality between the two groups will be rejected if the two-tailed *p*-value is < 0.05.

Binary secondary outcomes (unplanned reoperation and readmission) will be analyzed with the same model approach as used for the primary outcome. For the time-to-event outcome length of stay, we will use a multilevel mixed-effects parametric survival model parameterized as an accelerated failure time model. Random and fixed factors will be used as described above. The results will be presented as the difference in days with 95% CIs. Length of stay will be censored at the time of death or transfer to another hospital. Depending on the number of in-hospital deaths, we will consider a competing risk regression as the primary analysis approach for this outcome. Differences between the groups will be evaluated using multilevel mixed-effects linear regression, adjusting for random and fixed factors as described above. The results will be presented as the mean difference with 95% CI.

We will report results in accordance with the 2010 Consolidated Standards of Reporting Trials (CONSORT) statement extension to cluster-randomized trials [41].

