#### (Periodic) safety reporting

An annual safety report (ASR/DSUR) containing relevant safety information from all sites is provided by the sponsor. Relevant safety information in this case means descriptive statistics of accumulating primary and secondary endpoint events pooled across trial arms. Pooling of trial arms is necessary to avoid multiple testing. The sponsor distributes the ASR/DSUR to all the participating Investigators. It is submitted once a year to the local ethics committee by the investigator.

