#### (Premature) termination of study

The sponsor may terminate the study prematurely according to certain circumstances, e.g.:○ Ethical concerns○ Insufficient participant recruitment○ Alterations in accepted clinical practice that make the continuation of the study unwise○ Early evidence of harm of the experimental intervention

Upon regular study termination, the Ethics Committee is notified within 90 days.

Upon premature study termination or study interruption, the Ethics Committee is notified within 15 days.

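### The futility rule counts a significant result in either direction, so a clear interim excess of deaths under StOP? can pass it, and nothing links that look to the harm ground for termination

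*Protocol article*

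**What the plan says.** - **Interim analyses.** One look takes place once endpoint data are complete for 200 clusters. For futility: "The conditional power for a statistically significant difference between the intervention and control groups at the end of the study will be estimated", from the data available at that time. Below 20%, termination is recommended and the Steering Committee decides. The section states that no interim analysis for safety or efficacy is done and that no independent monitoring board is set up for that reason.
- **Statistical method for primary and secondary outcomes.** "The primary null hypothesis of no difference in mortality between the two groups will be rejected if the two-tailed *p*-value is < 0.05".
- **Objectives.** "The primary hypothesis is that the consistent use of the StOP?-protocol by the main surgeon reduces patient mortality within 30 days after an operation".
- **(Serious) adverse events.** Serious adverse events are not routinely recorded; the primary and secondary endpoints carry the safety information instead.
- **(Periodic) safety reporting.** The annual report contains "descriptive statistics of accumulating primary and secondary endpoint events pooled across trial arms".
- **(Premature) termination of study.** One listed ground is "Early evidence of harm of the experimental intervention".

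**The concern.** A futility rule should ask whether the trial can still show what it set out to show. Here that is fewer deaths. The stated quantity is the chance of any significant difference under a two-tailed test. It rises as the interim result moves away from no effect on either side, so a marked excess of deaths in the StOP? arm can look promising.

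Two things are at stake. As a futility rule it can retain a trial whose chance of showing benefit is close to nil. As a matter of oversight, this is the only planned comparison of the arms before the end, the endpoint is death, and the text does not say that an unfavourable result at this look should be considered under the harm ground for termination.

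**Working it through.** **Inputs (protocol article, Sample size calculation and Interim analyses).** Control mortality: "use this number (1.8%) for the event rate in the control group". Target odds ratio (OR) 0.5, about 0.9%. ICC 0.024, mean cluster size 24, coefficient of variation 0.5, 200 clusters per arm, two-sided 0.05. Interim at 200 of 400 clusters, so information fraction t = 0.5, assuming equal information per cluster. Futility threshold 20%.

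**Step 1: reproduce the stated power.** Design effect = 1 + (24 × (1 + 0.5²) − 1) × 0.024 = 1 + 29 × 0.024 = 1.696. Effective number per arm = 200 × 24 / 1.696 = 2,830. The two-proportion power for 1.8% against 0.9% is 83.5%. The article says "we will achieve 84% power at a significance level of 0.05 (two-sided"), so the inputs are read correctly.

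**Step 2: interim z.** The effective number per arm at the look is 2,830 / 2 = 1,415. With p₀ = 0.018 and p₁ from the OR,

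z = −ln(OR) / √[1/(1,415 p₀(1−p₀)) + 1/(1,415 p₁(1−p₁))], positive for benefit.

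At OR 1.5, p₁ = 0.0268 and z = −0.405 / 0.259 = −1.565.

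**Step 3: conditional power.** The final z has mean z√t + θ(1−t) and standard deviation √(1−t), where θ is the drift assumed for the remaining clusters. Benefit is a final z above 1.96 and harm a final z below −1.96. The wording covers the sum of the two. Three choices of θ are common: current trend (θ = z/√t), no effect (θ = 0) and the target effect (θ = 1.96 + 0.994 = 2.954, from 84% power).

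Example, current trend at OR 1.5: harm part = Φ((1.565/0.7071 − 1.96)/0.7071) = Φ(0.358) = 64%. The benefit part is practically 0%.

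| Interim OR | z | Either direction, current trend | Benefit only, current trend | Either direction, no effect in remainder | Either direction, target effect in remainder |
|---|---|---|---|---|---|
| 1.1 | −0.345 | 1.9% | <0.1% | 0.9% | 15.2% |
| 1.25 | −0.83 | 13% | <0.1% | 2.6% | 6.5% |
| 1.5 | −1.565 | 64% | <0.1% | 11% | 1.3% |
| 1.75 | −2.22 | 95% | <0.1% | 29% | 0.6% |
| 2.0 | −2.81 | 99.8% | <0.1% | 52% | 2.1% |
| 2.5 | −3.84 | 100% | <0.1% | 86% | 15.4% |

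Under current trend the 20% line on the harm side is crossed at z = −0.965, an OR of about 1.29.

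**Step 4: chance of passing the look, current trend.** As worded, the trial passes if z is below −0.965 or above 0.965. Defined for benefit, it passes only if z is above 0.965.

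- True OR 1.5 (mean z −1.565): Φ(0.600) + [1 − Φ(2.530)] = 72.6% + 0.6% = about 73%, against 0.6%.
- True OR 1.25 (mean z −0.83): 44.6% + 3.6% = about 48%, against about 4%.
- True OR 0.5 (mean z 2.01): the harm-side part is Φ(−0.965 − 2.01) = Φ(−2.98) = 0.1%. A benefit-only definition therefore loses almost nothing when the target effect is true.

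**Step 5: larger clusters.** At the target average of 30 per cluster the design effect is 1 + (30 × 1.25 − 1) × 0.024 = 1.876, and the effective number per arm is 6,000 / 1.876 = 3,198. At OR 1.5, z = −1.565 × √(3,198/2,830) = −1.66. Conditional power is about 71% and the chance of passing about 76%.

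**The case against.** The best defence is that the direction follows from context: the sentence is about futility, the hypothesis is a reduction in deaths, and the target is an OR of 0.5. A full protocol or analysis plan may also state the direction and the assumed effect. This is a plausible account of intent. It does not remove the point, because the published rule names a difference between groups and projects to a two-tailed test. Read literally, it can give the wrong recommendation.

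The second defence is stronger and stands as a limit. The article does not name the effect assumed for the remaining clusters. Current trend is the natural reading of a quantity estimated from interim data, especially since the ICC recalculation in the same section says explicitly that it keeps the original assumptions. With no effect assumed for the remainder, an interim OR of 1.5 would stop. With the target effect assumed, every harm trend in the table would stop.

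A reader might infer more than the documents support:

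- *That every harm trend passes.* It does not. Under current trend, an interim OR between 1.0 and about 1.29 falls below 20%.
- *That the problem is larger.* Ignoring clustering (2,400 operations per arm, z about −2.04 at OR 1.5) gives conditional power near 90% and a passing probability near 86%. The planned design effect brings these down to 64% and 73%.
- *That the rule orders continuation.* The text only recommends stopping below 20%; continuing above it is implied. The Steering Committee decides, and the sponsor may stop on other grounds.
- *That no step can produce evidence of harm.* This is too strong. Estimating conditional power requires the mortality comparison by arm, so the evidence would exist at this look. What is missing is a stated route from it to the termination ground.

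Having no formal safety analysis or monitoring board is a reasoned choice in the article and is not challenged here. The final test's type I error is unaffected.

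**Conclusion.** The concern holds in this limited form. The futility quantity has no direction while the hypothesis does. Under the current-trend reading, a clear excess of deaths (interim OR above about 1.29) would not meet the futility criterion. At a true OR of 1.5 the trial passes with probability about 73% instead of about 0.6%; at 1.25, about 48% instead of about 4%. With no effect assumed for the remaining clusters, the problem is confined to stronger trends (29% at an interim OR of 1.75, 52% at 2.0). With the target effect assumed, it does not arise for the trends computed.

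The sections on interim analyses, periodic safety reporting and premature termination also do not fit together. Early harm is a ground for stopping, yet the one comparative look is declared not to be a safety analysis and the annual report pools the arms.

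The figures rest on 1.8% control mortality, the planned ICC and cluster sizes, half the information at the look, and a normal approximation. This is more than a missing detail: a stated rule on a mortality endpoint can recommend wrongly, and the correction is small. It should be made before the interim look.

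**What to change.** 1. Define conditional power as the probability of a significant final result in favour of StOP? (OR below 1 with two-sided p < 0.05).
2. Name the effect assumed for the remaining clusters. If more than one assumption is shown, say which one the 20% threshold applies to.
3. Reconcile the three sections on interim analyses, periodic safety reporting and premature termination. State that mortality by arm from this same look is reported to those who decide on termination, so that the harm ground can be assessed, and name who sees it.

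The cost is a few sentences. No new data are needed, because the look already compares the arms. A look that can stop only for lack of benefit or for harm spends no efficacy alpha. The price is a higher chance of stopping when the interim trend is unfavourable. Under the target effect that added chance is about 0.1%. With no true effect the chance of passing falls from about 33% to about 17% (current trend: twice, against once, 1 − Φ(0.965) = 16.7%), which is what a futility rule is meant to do.
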